# The utility of pericapsular nerve group (PENG) block versus intrathecal morphine for postoperative analgesia in anterior approach total hip arthroplasty: a multicentre triple blinded randomised controlled trial protocol

**DOI:** 10.1186/s13063-025-09127-8

**Published:** 2025-09-29

**Keywords:** Total hip replacement, Total hip arthroplasty, PENG block, Pericapsular nerve group block, Regional anaesthesia, Intrathecal morphine, Analgesia

## Abstract

**Background:**

The pericapsular nerve group (PENG) block is a novel regional technique for hip analgesia. Traditionally, intrathecal morphine has been administered for analgesia in hip fracture surgery. Compared with intrathecal morphine, the PENG block may provide superior or equivalent pain score reduction with a more favourable side effect profile and superior patient satisfaction.

**Methods:**

This is a multicentre blinded randomised controlled trial (RCT) that is being conducted at present at two large teaching institutions in Australia. The pericapsular nerve group block (PENG block) shall be compared to low-dose intrathecal morphine for analgesic effect in elective total Hip arthroplasty via the direct anterior approach. Primary outcome shall be dynamic pain score evaluation at 3 and 24 h postoperatively.

**Discussion:**

This is the protocol of our RCT which is currently in the early stages of active recruitment.

**Trial registration:**

Ethics approval was obtained from the Southern Area Local Health Network prior to recruitment of the first patient. This trial was prospectively registered prior to initiation on the Australian and New Zealand Clinical Trials Registry. Australian New Zealand Clinical Trial Registry, ACTRN12623001309673P, 15/12/23, https://www.anzctr.org.au/Trial/Registration/TrialReview.aspx?id=386688&showOriginal=true&isReview=true.

**Supplementary Information:**

The online version contains supplementary material available at 10.1186/s13063-025-09127-8.

## Introduction

Total hip arthroplasty (THA) is one of the most successful operations of the century [1]. In Australia, it has been estimated that the rate of Hip arthroplasty is approximately 171 per 100,000 population [2]. Based on data collected by the Australian Orthopaedic National Joint Replacement Registry, the anterior approach to THA constituted approximately 28% of all THAs performed between 2015 and 2022 [3]. The anterior approach is increasingly popular amongst arthroplasty surgeons [4], as it has been associated with lower rates of revision for infection and instability [3].

THA is associated with significant postoperative pain and opioid consumption [5]. Hence, optimisation of perioperative pain management in these patients via a multimodal approach is vital to facilitate early mobilisation and discharge [6], whilst reducing the incidence of postoperative complications [7–9]. Current procedure-specific postoperative pain management (PROSPECT) guidelines for THA advocate for anaesthesiologists to consider 100 µg of intrathecal morphine as a component of spinal anaesthesia for the provision of perioperative analgesia [10]. Although effective as an analgesic, intrathecal morphine has been associated with adverse reactions, such as nausea, vomiting and pruritus, which in turn, may delay mobilisation [11].

The pericapsular nerve group (PENG) block was first described by Girón-Arango et al. in 2018 for regional hip anaesthesia [12]. It is usually thought to be purely sensory blockade, although this is not always the case [9]. Previous studies have shown that both PENG block and intrathecal morphine provided superior analgesic outcomes when compared to placebo; however, there have been no comparative studies between these two modalities [8, 13]. In our study, we will compare the PENG block to intrathecal morphine, which is the current standard of care in our institution, for the provision of perioperative analgesia, measured using numerical pain scale at 3 and 24 h postoperatively, in patients undergoing anterior approach THA.

## Methods

This is a multicentre triple-blinded pragmatic parallel design randomised controlled superiority trial that will be conducted at two teaching hospitals, Noarlunga Health Services (NHS) and Flinders Medical Centre (FMC), both located in Adelaide, Australia. We have obtained ethical approval from the relevant Human Research Ethics Committee prior to begin and shall obtain written informed consent from all participants. This study will conform to the recommendations of Consolidated Standards of Reporting Trials (CONSORT). All researchers have a current Good Clinical Practice certificate from within the last 3 years.

### Patient population

All adult patients above the age of 18 years old presenting at these two large tertiary academic hospitals for primary elective anterior approach THA under spinal anaesthesia will be invited to participate in this study. Included participants must be able to provide informed consent and reliably report symptoms to the research team. We will exclude patients who are (1) unable to provide first party consent (e.g. due to cognitive impairment or language barrier), (2) procedure not performed via an anterior approach, (3) contraindications for any of the following: spinal, intrathecal morphine or PENG block (e.g. therapeutic anticoagulation, anaphylaxis to local anaesthetics or morphine), (4) patient refusal of spinal anaesthesia and/or regional analgesia, (5) clinical indications for general anaesthesia rather than spinal anaesthesia and (6) THA performed for pathological lesions.

All patients scheduled for primary elective direct anterior approach Hip arthroplasty will be approached for potential inclusion during their preoperative assessment at preadmission clinic or immediately afterwards. This strategy is to maximise recruitment opportunities; we estimated that we can achieve our targeted trial enrolment in 8 months based on historical data and have included a contingency for an additional 1-month recruitment in our trial. This is normally held 2–4 weeks preoperatively. Patients can consent to participate up until the day of surgery itself. Consent will be undertaken by a trained research nurse separate to the patients surgical and anaesthetic providers. It will be stressed that non-participation will not alter their treatment and consent can be withdrawn at any point in time. A patient information sheet will also be provided. Participants will be given written information, the opportunity to ask questions and the right to withdraw at any time without consequence. Participant retention in the trial is expected to be high due to the short-term nature of in-hospital only follow-up. Descriptive data will be collected on any reason for participant discontinuation and protocol deviations.

### Study intervention

Anaesthetic technique will be standardised to a spinal anaesthesia with 0.5% isobaric bupivacaine (range 10–15 mg), followed by a single intravenous dose of 8 mg dexamethasone. Following the administration of spinal anaesthesia, the allocated analgesic technique was performed. In patients allocated to the intrathecal morphine group, a sham PENG block will be performed. However, in the PENG group, a sham injection of intrathecal morphine will not be added. Prior to patient inclusion in the trial, it will be confirmed that no contraindications to either technique exist such that there will be no need to modify allocated interventions for individual participants. A research nurse with a copy of the trial protocol will be present on the day of surgery for each participant to ensure compliance with the study protocol and a senior investigator allocated to be available for all trial queries. The research nurse will maintain blinding by leaving theatre during the administration of the trial intervention.

#### PENG group

The block will be placed using ultrasound guidance with a curvilinear probe (2.5–5 MHz). Twenty millilitres of ropivacaine 0.5% (100 mg) prepared by the anaesthesiologist performing the block will be used. The area is aseptically prepped and draped. The curvilinear probe will be placed transversely, medial to the anterior inferior iliac spine with the medial end of the probe rotated in a caudad direction to align to the superior pubic ramus. A 100-mm Sonoplex needle will be inserted in-plane under ultrasound guidance. Twenty millilitres of local anaesthetic will be injected as a plane block between the psoas fascia and superior pubic rami. A cross shall then be drawn on the skin with surgical marker to disguise the presence of a puncture site.

#### Intrathecal morphine group

In addition to the spinal anaesthesia already infiltrated, a further 100 mcg of morphine will be administered. The sham block will be then simulated by the anaesthesiologist by prepping, scanning and draping as per PENG block protocol. The probe and a blunt needle, with a 20-mL syringe filled with saline attached, were held against the skin, similar to the PENG block, and a sufficient pause to simulate the block being performed will be conducted, without penetration of skin or actual administration of any medicine. Likewise, a cross shall then be drawn on the skin with surgical marker to disguise the absence of a puncture site.

### Preoperative education, surgical technique and postoperative management

Preoperatively, patients will be educated on the procedure and expected postoperative rehabilitation. On the day of surgery, following the allocated anaesthesia regimen, the patient is positioned supine, prepped and draped for surgery. Prophylactic antibiotics and tranexamic acid (TXA) will be administered prior to skin incision. The surgery will be conducted by a fellowship-trained orthopaedic surgeon utilising the direct anterior approach. Preparation of the acetabulum and femur will be performed, followed by trial and definitive implant insertion. Routine pericapsular local infiltration analgesia will be performed in all patients, utilising 100 mL of 0.2% ropivacaine with 1 mg adrenaline. Postoperative analgesia regime was standardised with regular paracetamol and NSAIDs if no contraindication and if needed tramadol, oxycodone and/or fentanyl on a nurse-administered basis. Additionally, postoperative antiemetics and antihistamines are also administered as required. All patients will receive two further doses of postoperative antibiotics and allowed to mobilise as tolerated. The urinary catheter will be removed within 24 h unless the patient has a long-term urinary catheter.

### Data collection and outcomes of interest

Baseline demographic information including age, gender, ethnicity, body mass index, type of residence, chronic opioid usage, residence type, ASA grade, Charlson Comorbidity Index, preoperative patient reported outcome measures (Oxford Hip Score, EQ-5D-5L Index, pain score), preoperative mobility status and comorbidities will be collected prior to randomisation. The type of prosthesis used, as well as intraoperative complications will be recorded accordingly. Overall evaluation is expected to take approximately 30 min of the participants’ time. No compensation will be offered. Timing of data collection is shown in Fig. 1. Data entry into the password-protected trial database will be performed by trained research nurses and checked by senior investigators. In accordance with institutional policy, data will be stored for 15 years on the secure hospital server with access available to senior investigators.

**Fig. 1 Fig1:**
[figure not shown]
SPIRIT formatted display of schedule for enrolment, intervention and assessments timing

#### Primary outcomes

The primary outcome of interest is the dynamic pain score at 3 and 24 h postoperatively. These scores are measured using a numerical pain scale from zero to ten.

#### Secondary outcomes

See Fig. 2.

**Fig. 2 Fig2:**
[figure not shown]
Secondary outcomes

### Recruitment, enrolment and randomisation

Patient recruitment will be performed by a research nurse, who would identify potential participants, as well as screening them against the eligibility criteria. Informed consent would then be obtained by the research team following discussions about the expected benefits, risks, trial commitments and uncertainties of each technique. This is separate to the surgical consent for the procedure itself.

Computer-generated random treatment assignment (sealedenvelope.com) on a 1:1 ratio with permutated blocks (randomly generated blocks of 2, 4 and 6) will be performed immediately prior to surgery by the anaesthetist. Allocation concealment will thus be maintained. The intervention will be blinded to the patient, surgical and treating team, and the research team involved in data collection. Ward nursing staff shall also be blinded and shall be advised to treat all study patients as if they have had intrathecal morphine for safety reasons. Only the anaesthetist performing the intervention and their assistant shall not be blinded.

This is a pragmatic study designed for high external generalisability. All relevant concomitant care deemed necessary by the treating physicians will be permitted and recorded. Participant retention is by nature expected to be high in this RCT as it is short-term perioperative only.

### Sample size calculation

We performed a retrospective case note review to determine the effect size required. As we had two primary outcomes, the larger of the two sample size calculations was utilised. Sample size calculation was then performed using G*Power (Düsseldorf, Germany) with two-sided significance level of 0.05 and 80% power. The sample size required to detect a mean difference in pain scores of 0.8 at 3 h postoperatively was 26 in each group, whereas that required to detect a mean difference in pain scores of 3.3 at 24 h postoperatively was 20 in each group. Accounting for 30% dropout or non-adherence rate, we arrived at a final sample size of 35 in each arm.

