### Statistical analysis

All statistical analyses will be performed using Stata version 18 (StataCorp, USA). The threshold for statistical significance in this study is set at 5%. As two primary outcomes are measured, a corrected *p* value threshold of 0.025, obtained using the Bonferroni correction technique, will be utilised when assessing these outcomes. Intention to treat analysis will be performed in all cases. Categorical variables will be displayed as frequency (percentage) and analysed using chi-squared test. Continuous variables will be assessed for normality using the Shapiro–Wilk test. Normally distributed data will be displayed as mean ± standard deviation and analysed using unpaired *t*-test. Continuous data that is not normally distributed will be displayed as median (range) and analysed using Mann–Whitney *U* test. Nonadherence to randomly assigned treatment may mean that the intention to treat analysis may misrepresent the true treatment effect. Therefore, a per-protocol analysis will be performed if there is greater than 10% crossover between groups. We do not plan on undertaking an interim data analysis due to the small sample size of the trial and the use of two routine clinical interventions.

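### The sample size is calculated at a two-sided 0.05 but each primary outcome is tested at 0.025, so 26 per group gives about 72% power at 3 h, not 80%

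*Protocol article*

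**What the plan says.** In the Protocol article, the Sample size calculation section states that the calculation was done in G*Power "with two-sided significance level of 0.05 and 80% power". It gives two results: the number needed for a "mean difference in pain scores of 0.8 at 3 h postoperatively was 26 in each group", and for a "mean difference in pain scores of 3.3 at 24 h postoperatively was 20 in each group". The rule for combining them is: "As we had two primary outcomes, the larger of the two sample size calculations was utilised". The 26 is then raised to 35 per arm for 30% dropout or non-adherence.

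The Statistical analysis section sets a different level for the same two outcomes: "a corrected *p* value threshold of 0.025, obtained using the Bonferroni correction technique, will be utilised when assessing these outcomes". Nothing in the article connects this threshold to the sample size calculation.

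**The concern.** Power depends on the significance level at which the test is judged. Here the level used for sizing (0.05) is twice the level used for testing (0.025). Taking the larger of two sample sizes gives each outcome at least its own required number, but it makes no allowance for the stricter threshold. If that is so, the 80% does not describe the test that will be carried out. The outcome most exposed is the 3 h pain score, because it sets the sample size and has no reserve. A null result at 3 h could then be read as coming from a trial with 80% power when the true figure was lower.

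**Working it through.** **Inputs from the article**
- Sample size calculation: two-sided 0.05; 80% power; difference 0.8 with 26 per group at 3 h; difference 3.3 with 20 per group at 24 h; 30% allowance; 35 per arm.
- Statistical analysis: 0.025 for each primary outcome; unpaired t-test if the data are normal.
- Recruitment, enrolment and randomisation: allocation "on a 1:1 ratio with permutated blocks".

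**Assumption.** The standard deviation is not stated; the article says only "We performed a retrospective case note review to determine the effect size required". I back-solve the standardised difference d = (mean difference)/SD from the plan's own figures and carry the range through.

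**Formula.** For a two-sample t-test with n per group, the degrees of freedom are 2n − 2 and the noncentrality is d√(n/2). Power is the probability that a noncentral t with these parameters exceeds the two-sided critical value in absolute size.

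**Step 1: reproduce the plan's 26.** Take d = 0.8 (SD = 1) and n = 26. The noncentrality is 0.8 × √13 = 2.884 on 50 degrees of freedom, and the critical value at 0.05 is 2.009. Power is 80.7%, and 26 is the smallest n that reaches 80%. More generally, 26 is the smallest adequate n at 0.05 for any d from 0.792 to 0.809 (SD 0.99 to 1.01). For 20 per group at 24 h, d lies between 0.909 and 0.934 (SD 3.53 to 3.63).

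**Step 2: change only the significance level.** At 0.025 the critical value on 50 degrees of freedom rises to 2.311. With the same d = 0.8 and n = 26, power falls to 71.6%. Over the whole range of d it is 70.7% to 72.6%.

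**Step 3: number needed for 80% at 0.025.** At 3 h, 31 per group when d = 0.8 (power 80.0%), and 31 to 32 over the range. At 24 h, 24 to 25 per group.

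**Step 4: power at 0.025 for the numbers that might be analysed.** The 30% allowance applied to 35 per arm leaves 35 × 0.7 = 24.5, so 24 or 25.

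| Analysed per group | 3 h, d = 0.8 | 3 h, range of d | 24 h, range of d |
|---|---|---|---|
| 24 | 67.5% | 66.6–68.6% | 79.4–81.7% |
| 25 | 69.6% | 68.7–70.6% | 81.3–83.5% |
| 26 | 71.6% | 70.7–72.6% | 83.0–85.1% |
| 31 | 80.0% | 79.2–80.9% | – |
| 35 | 85.2% | 84.4–86.0% | 93.2–94.4% |

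**Step 5: loss that 35 per arm can bear.** Keeping 31 analysed allows (35 − 31)/35 = 11.4% loss. Keeping 32 allows (35 − 32)/35 = 8.6%.

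**Check on a mislabelled level.** For 26 per group to be a calculation at 0.025 with 80% power, d would have to be about 0.877 (SD about 0.91). The text says 0.05, and d = 0.8 at 0.05 returns 26 exactly, so this reading is unlikely.

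**The case against.** The strongest reply is that the enrolled sample largely absorbs the error. With all 35 per arm analysed, 3 h power at 0.025 is about 85%, above the 80% promised. The article expects high retention because follow-up is short and in hospital. Its 30% allowance covers non-adherence as well as dropout, and under intention to treat, non-adherent patients with pain scores stay in the analysis. The figure of about 67% therefore assumes that the whole allowance is lost. It also contains a separate effect: 24 per group is below 26 in any case, and at 0.05 its power would already be 77.4%. The level itself accounts for the fall from 77.4% to 67.5%.

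This stands as a limit on the size of the problem. It does not make the stated calculation right. The step from 26 to 35 was made for dropout and non-adherence, not for multiplicity. Non-adherent patients kept in the analysis preserve n but may dilute the difference.

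Two further points also stand. At 24 h the shortfall exists only at the nominal 20 per group, which no one plans to analyse. And the article does not say whether one or both outcomes must succeed. If one is enough, the chance of at least one success at 26 per group is no lower than the 83% to 85% for 24 h, under the plan's own effects. The 80% is therefore missed for the 3 h outcome, not necessarily for the trial as a whole. But the article sizes each outcome separately, so the 80% has to be judged outcome by outcome.

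**Conclusion.** The concern holds. The level in the calculation is not the level of the test, and the article does not reconcile them. At the stated 26 per group, power for the 3 h outcome is 71% to 73%, so the risk of missing the assumed effect is 27% to 29% rather than 20%. For 80% at 0.025, 31 to 32 analysed per group are needed. Enrolling 35 per arm meets this only if no more than about 9% to 11% are lost from the analysis.

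The result does not depend on knowing the standard deviation, because any value consistent with 26 per group at 0.05 and 80% gives the same answer within about one percentage point either side of 71.6%. It does rest on an unpaired t-test with equal groups. If the Mann–Whitney test is used on roughly normal data, about 5% more are needed, or about 33 per group at 0.025. The Bonferroni threshold itself is valid, and type I error control is not affected.

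**What to change.** Redo the calculation at two-sided 0.025 for both outcomes and state the standard deviations taken from the case note review. If these agree with the back-solved values, report that 31 to 32 analysed per group are needed at 3 h and 24 to 25 at 24 h. Then state 3 h power against the number analysed: about 85% with 35 per arm, 80% with 31 to 32, and about 67% to 71% if the full 30% is lost.

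The cost is one recalculation and a few sentences, and the stated power becomes less favourable. The analysis and trial conduct do not change, and no unblinded data are needed. Additional patients would be required only if the sponsor wants 80% power at 3 h to survive a full 30% loss: 31/0.7 = 44.3 and 32/0.7 = 45.7, so 45 to 46 per arm. Otherwise the correction should be made before results are reported, so that a null 3 h result is read against the right power.

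### The two sample-size targets imply SDs of about 1.0 and 3.6 on the same 0–10 pain scale; the units of the 3 h target and both SDs need to be stated and the power restated

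*Protocol article*

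**What the plan says.** The Sample size calculation section of the protocol article describes both targets in the same terms. For 3 h it reads "The sample size required to detect a mean difference in pain scores of 0.8", with 26 per group as the answer; the other target is a "mean difference in pain scores of 3.3 at 24 h postoperatively was 20 in each group". Both calculations use a "two-sided significance level of 0.05 and 80% power". The larger requirement, the one for 3 h, is carried forward and raised to 35 per arm for 30% dropout or non-adherence.

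The section names the source of the assumptions ("We performed a retrospective case note review to determine the effect size required") and the software, but gives no SD for either time point. The Primary outcomes section puts both time points on one scale: "These scores are measured using a numerical pain scale from zero to ten". The Statistical analysis section tests each primary outcome at 0.025, by unpaired t-test or, for non-normal data, the Mann–Whitney test.

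**The concern.** Once the difference, the group size, alpha and power are fixed, the SD is fixed too. The two statements can therefore be inverted, and the SDs they imply differ about 3.6-fold for the same score in the same patients, 21 hours apart. The larger one exceeds the SD of a score spread evenly over 0 to 10. The smaller one is almost exactly 1, the value at which a raw difference and a standardised difference are numerically identical. A reader therefore cannot tell whether 0.8 is in scale points or in SD units.

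This matters because the 3 h calculation sets the size of the trial. If 0.8 is in points and the 3 h SD is well above 1, power for that difference is far below 80%. A non-significant 3 h result could then be read as evidence against a 0.8-point difference that the trial had little chance of detecting.

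**Working it through.** **Inputs.** From Sample size calculation: two-sided alpha 0.05; power 80%; 0.8 with 26 per group (3 h); 3.3 with 20 per group (24 h). From Recruitment, enrolment and randomisation: 1:1 allocation. From Statistical analysis: unpaired t-test, threshold 0.025 for each primary outcome. The SD is not stated.

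**Formula.** For n per group and standardised difference d = difference/SD, the two-sample t statistic is noncentral t with 2n − 2 degrees of freedom and noncentrality d√(n/2). Power is the probability that it falls beyond the two-sided critical value.

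**The plan's own figures.** Neither n can be reproduced as a raw difference without an SD. Read as a standardised difference, 0.8 gives power 79.1% with 25 per group and 80.7% with 26, so the smallest adequate n is 26. The match is tight: d = 0.79 needs 27 and d = 0.81 needs 25. The 3.3 cannot be a standardised difference, because d = 3.3 would need only 3 per group.

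**Implied SDs.**
- n = 26 is the smallest adequate size for d from 0.792 to 0.809. SD = 0.8/0.809 to 0.8/0.792 = 0.99 to 1.01.
- n = 20 is the smallest adequate size for d from 0.909 to 0.934. SD = 3.3/0.934 to 3.3/0.909 = 3.53 to 3.63.
- For comparison, a uniform spread over the integers 0 to 10 has SD √((11² − 1)/12) = √10 = 3.16.

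**Does the method matter?** The contrast stays under each alternative tried:

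| Method | Implied SD, 3 h | Implied SD, 24 h |
|---|---|---|
| t-test, two-sided 0.05 | 0.99–1.01 | 3.53–3.63 |
| Normal approximation | 1.01–1.03 | 3.63–3.72 |
| One-sided 0.05 | 1.12–1.14 | 4.01–4.12 |
| Two-sided 0.025 | 0.89–0.91 | 3.18–3.27 |
| Mann–Whitney (efficiency 0.864 to 3/π) | 0.94–0.99 | 3.36–3.54 |

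**Power for 0.8 points, if 0.8 is in points.** The SDs are assumptions, since none is stated. Each cell gives power at alpha 0.05, then at 0.025 in brackets.

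| Assumed 3 h SD | 26 per arm | 35 per arm |
|---|---|---|
| 1.0 | 80.7% (71.6%) | 91.0% (85.2%) |
| 1.5 | 47.1% (35.7%) | 59.5% (47.9%) |
| 2.0 | 29.3% (20.2%) | 37.8% (27.5%) |

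At SD 2.0, 80% power at alpha 0.05 would take 100 per group.

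**Detectable difference with 80% power at 0.025.** This is 0.88 SD with 26 per arm and 0.75 SD with 35. At SD 1.0 that is 0.88 and 0.75 points; at SD 2.0 it is about 1.75 and 1.5 points.

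**The case against.** The strongest reply is that no arithmetic error has been shown. Each statement is correct for some SD. Saying that 26 is the answer for d = 0.8 is the same as saying that the SD is 1.0, so the match cannot separate a mislabelled effect size from a raw difference with a small SD. That stands. A reader might infer that 0.8 is certainly a Cohen's d and should simply be relabelled; the document does not support that.

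There is also a plausible reason for a small SD at 3 h. Patients have recently had spinal bupivacaine, dexamethasone and the allocated technique (Study intervention), and ropivacaine infiltration (Preoperative education, surgical technique and postoperative management). Scores may sit near zero with little spread, and spread may be wider by 24 h, when opioids are given as needed. This makes an SD near 1.0 possible at 3 h. It does not account for 3.6 at 24 h, which is unusual, though not impossible (the maximum on a 0–10 scale is about 5). Relabelling 0.8 does not account for it either.

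Two further points stand. Power should not be judged only after full attrition: 35 per arm are enrolled and high retention is expected, so both sizes are shown. And a condensed article may leave the SDs to the full protocol, so their absence alone is not the fault. The point is that the figures printed here do not sit together.

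**Conclusion.** The point holds as a discordance between stated figures, not as a proven mislabelling. Given the stated alpha and power, the targets require SDs of about 1.0 at 3 h and 3.6 at 24 h, and no reasonable choice of test removes the contrast. The stated 80% power for 0.8 points depends on a 3 h SD of about 1.0, which the article does not give.

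A reader might also infer that the trial is underpowered at 3 h. That depends on the unknown SD. At SD 1.0 with all 35 per arm retained, power is 85% even at the 0.025 threshold. With 26 per arm it is 72%, because the calculation used 0.05; that mismatch is a separate matter and adds no weight here beyond fixing the threshold at which power should be restated. The low figures at SD 1.5 and 2 rest on assumed values.

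This should be fixed, because the 3 h target sets the trial size and a null result would be read against it. It does not affect the trial's conduct or its planned analysis.

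**What to change.** Return to the case-note review and the sample-size output, and reconcile the two targets:

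1. State whether 0.8 is in scale points or SD units, and which SD was used at 3 h and at 24 h.
2. Restate, at the 0.025 threshold, either the power or the minimum detectable difference in points, for both 26 and 35 per arm (0.88 SD and 0.75 SD at 80% power).
3. Do not describe the trial as having 80% power for 0.8 points unless the 3 h SD is confirmed to be about 1.0.

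The cost is a check of existing output and a few rewritten sentences. The stated power or detectable difference may look less favourable. No extra patients are needed. The correction is best made before the 3 h result is interpreted.

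### 35 per arm does not cover the stated 30% allowance on 26 per group (38 would be needed), and a headcount allowance does not cover non-adherent patients kept under intention to treat

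*Protocol article*

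**What the plan says.** All the inputs are in the protocol article, under Sample size calculation. The calculation uses a "two-sided significance level of 0.05 and 80% power". The number needed to "detect a mean difference in pain scores of 0.8 at 3 h postoperatively was 26 in each group", and the number needed to "detect a mean difference in pain scores of 3.3 at 24 h postoperatively was 20 in each group". With two primary outcomes, "the larger of the two sample size calculations was utilised", so 26 per group governs. The section ends: "Accounting for 30% dropout or non-adherence rate, we arrived at a final sample size of 35 in each arm". It gives no SD and does not divide the 30% between dropout and non-adherence.

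Under Statistical analysis: "Intention to treat analysis will be performed in all cases". The same section warns that non-adherence can distort an intention-to-treat estimate, and it adds a per-protocol analysis if crossover exceeds 10%. It tests each primary outcome at 0.025.

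Two other sections expect little loss to follow-up. Patient population says "Participant retention in the trial is expected to be high due to the short-term nature of in-hospital only follow-up", and Recruitment, enrolment and randomisation says "Participant retention is by nature expected to be high in this RCT as it is short-term perioperative only".

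**The concern.** The target is presented as the result of a 30% allowance on 26 per group, and it is not. A reader who divides 26 by 0.70 gets a larger number and cannot tell whether the 30%, the 26 or the 35 is the figure that was meant.

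The second difficulty is one of kind. Dividing by one minus a rate is right for patients whose outcome is missing. A patient who does not receive the allocated technique but has a pain score recorded is not missing under intention to treat. That patient keeps the headcount up and pulls the two arms together. A single pooled allowance handles only the first kind of loss, so the power of the primary analysis under the stated assumption cannot be read from the article.

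**Working it through.** **Inputs from the article.** Evaluable n per group: 26 (3 h) and 20 (24 h). Two-sided alpha 0.05, power 80%. Pooled allowance 30%. Target 35 per arm.

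**1. Can 35 be reproduced?** For missing outcomes, n per arm = n evaluable / (1 − r).
- 26/0.70 = 37.1, so 38 per arm.
- On the total: 52/0.70 = 74.3, so 75, against the planned 70.
- The common mistake, 26 × 1.30 = 33.8, gives 34.
- A 25% allowance, 26/0.75 = 34.7, gives 35.

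The standard formula does not give 35 at 30%. The article does not show how 35 arose, so the last two lines are only possible explanations.

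**2. What does 35 deliver?**
- Evaluable after 30% loss: 35 × 0.70 = 24.5, against 26 required.
- Largest loss that leaves 26: 1 − 26/35 = 25.7%.
- 24 h outcome: 20/0.70 = 28.6, so 29, which is below 35. This outcome is covered for pure dropout.

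**3. Power lost at 3 h.** The SD is not stated, so the standardised difference d has to be inferred. For a two-sample t-test at 0.05 and 80% power, exactly 26 per group corresponds to d = 0.792 and exactly 25 to d = 0.809. Any d between about 0.79 and 0.81 therefore rounds up to 26. With a raw difference of 0.8 this implies an SD of about 0.8/0.792 = 1.01 to 0.8/0.809 = 0.99. This is an assumption, not a figure from the article.

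Power at 24 per arm, alpha 0.05: 76.6% (d = 0.792) to 78.3% (d = 0.809).

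**4. Non-adherence under intention to treat.** Assumption for illustration: a fraction c of patients is non-adherent in a way that removes their contribution to the difference, so d becomes d(1 − c). A fraction r has no outcome. Then n per arm = 26 / [(1 − c)² (1 − r)].

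| Dropout r | Non-adherence c | n per arm needed | Power at 35 per arm, alpha 0.05 |
|---|---|---|---|
| 30% | 0% | 26/0.70 = 37.1 → 38 | 78–79% (24.5 evaluable) |
| 15% | 15% | 26/(0.7225 × 0.85) = 42.3 → 43 | 72–74% |
| 0% | 30% | 26/0.49 = 53.1 → 54 | 63–65% |

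The power ranges run over d = 0.792 to 0.809. The article states no split, so the second and third rows show sensitivity and are not estimates.

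**5. At the threshold used in the analysis.** Testing at 0.025 needs 30.4 to 31.6 per group over the same range of d, so 31 to 32. Then 35 per arm tolerates 1 − 31/35 = 11.4% down to 1 − 32/35 = 8.6% loss. This comes from the separate mismatch between the alpha used for sizing and the alpha used for testing. It is given only so that the restated figures can be carried over.

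**The case against.** The strongest reply is that the slip hardly matters. It is 3 patients per arm and 2 to 3 points of power on one of two primary outcomes. It bites only if loss of outcome data exceeds 25.7%, in a short in-hospital trial. That is right about the size. It does not make the printed derivation correct.

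A second reply is that the protocol does not ignore non-adherence. It plans a per-protocol analysis above 10% crossover, and a headcount allowance suits an analysis that drops non-adherent patients. This stands for that analysis. But the per-protocol analysis is conditional, while intention to treat applies in all cases, and for intention to treat the allowance does not address dilution.

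Third, the 63–65% figure is an extreme. Randomisation takes place immediately before surgery, contraindications are checked before inclusion and a research nurse attends to ensure compliance. Nothing in the article suggests that 30% would miss a single intervention given in theatre. This is accepted, and the figure is labelled as a worst case.

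Fourth, a reader might infer that the 30% contradicts the two statements expecting high retention. The documents do not support that. Those statements concern retention only, whereas the 30% covers dropout and non-adherence together and can be a deliberately cautious allowance. At most, its basis should be explained.

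Fifth, naming the loss that 35 can absorb could be seen as fitting the assumption to the number. The objection has force if the figure is presented as the original planning assumption. It has none if it is reported as the capacity of the chosen size.

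**Conclusion.** The point holds in two parts.

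The arithmetic is wrong as printed: 30% on 26 gives 38 per arm, not 35. This needs no assumption beyond the article's own inputs. Its effect is modest: about 77–78% power at 3 h with 24 completers, given d of 0.79–0.81 and alpha 0.05, and no shortfall at 24 h for pure dropout.

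The allowance also does not fit the primary analysis, because non-adherent patients stay in and dilute the difference. The direction is certain. The size depends on a split that is not stated and on how completely non-adherence removes the effect.

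A reader might go further and conclude that the trial must recruit more patients because of this slip. That does not follow: 35 per arm meets the 26-per-group requirement at alpha 0.05 as long as no more than 25.7% of outcomes are missing and dilution is negligible. The tighter tolerance of about 9–11% arises only at 0.025 and belongs to the alpha mismatch.

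**What to change.** Keep 35 per arm and correct the text:

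- State that 35 per arm retains 26 evaluable per group with up to about 25% missing outcomes at alpha 0.05, or keep the 30% and state that 3 h power then falls to about 77–78%. Present the 25% as what the sample size can absorb, not as a forecast.
- Apply the 1/(1 − r) inflation to missing outcomes only.
- State a non-adherence rate separately, with its reason, and report intention-to-treat power at that rate.
- Give the SD or standardised difference behind the 26, so that these figures no longer rest on an inferred d.
- Explain the basis of the 30% if it stays, since retention is expected to be high.
- When the alpha mismatch is corrected, restate everything at 0.025: 31 to 32 evaluable per group, so 35 tolerates about 9–11% loss, depending on d.

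The cost is wording and a slightly less favourable stated figure. No patients are added and no trial procedure changes.
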